### Power of the study

According to the published literature and own experience at the VU university medical center a difference in respiratory infections of 28% is found between the traditional open procedure (57%) and the MIE procedure (29%) [6,7,9,13-15]. To demonstrate this difference of 28%, using a alpha = 0.05 and beta = 0.80, two groups of 48 patients are needed. This is based on a two-sided significance level (alpha) of 0.05 and a power of 0.80. Estimating that approximately 20% of the patients may be excluded, 60 patients will be randomized per arm.

### Inclusion criteria

Candidates to be included in this study are all patients with a histologically proven squamous cell carcinoma, adenocarcinoma or undifferentiated carcinoma of the intrathoracic esophagus and Siewert I junction tumors which are surgically resectable (T1-3, N0-1, M0) and treated by neoadjuvant therapy. The age of the patients must be ≥ 18 and ≤ 75 years. Moreover, the included patients must have a European Clinical Oncology Group (ECOG) performance status of 0, 1 or 2; and their written informed consent is obligatory.

### Exclusion criteria

Patients are excluded as subjects if there is a carcinoma of the cervical esophagus or have undergone prior thoracic surgery or no informed consent is provided. An exclusion list is maintained by all participating centers in order to analyze the quality of the randomization rate.

### Participating surgeons and clinics

To prevent surgeon bias, the open and laparoscopic operations have to be performed by experienced surgeons in conventional esophageal resections with experience of at least 10 minimally invasive esophagectomies. Duration of operation, conversion to open surgery, and complication rate may be related as factors to experience, yearly volume and the learning curve of the participating surgeon [16]. The surgeons in the three Dutch centers have been proctored by the two experienced minimally invasive surgeons of the VU university medical center. After the fist five patients operated on by an combined team, the video's of the last two of a series of 15 patients who had undergone a minimally invasive approach were examined by the VU university medical center surgeons. Only the surgeons with sufficient experience and skill after the proctoring series are allowed in participation in the trial. The surgeons of the two other centers are already well experienced in minimally invasive esophagectomy. In order to prevent institution bias, only hospitals with high volume (>20 esophagectomies/year) will participate in this trial.

Six European academic and non-academic centers will participate in the study: Academic Medical Center, Amsterdam, the Netherlands; Atrium Medical Center, Heerlen, the Netherlands; Canisius Wilhelmina Ziekenhuis, Nijmegen, the Netherlands; Hospital Universitari de Girona, [name], Girona, Spain; I.R.C.C.S. Policlinico San Donato, Milan, Italy; and VU university medical center (Vumc), Amsterdam, the Netherlands.

### Randomization

The patient will be informed about the trial at the outpatient clinic. When informed consent is obtained, the patient will be randomized at the outpatient clinic. Randomization is performed per center by an internet randomization module maintained by coordinators at the VUmc. As some heterogeneity is expected, e.g. difference in type of neoadjuvant therapy protocol, randomization will be stratified for each center. A flowchart of the study protocol is seen in Figure 1.

**Figure 1 F1:**
[figure not shown]
**TIME-trial flowchart**.

### Data collection and statistics

Data are transcribed via datasheets on paper and sent to the VUmc by surface mail. Data are collected daily until the day of discharge. The quality of life questionnaires (SF-36 and EORTC-OES18) are completed by the patient starting preoperatively and post-operatively at 6 weeks, 3 months, 6 months, and at 1 year. There will be regular contact between the study-coordinators and the participating centers. One research fellow will monitor the data of all included patients. Using a SPSS database containing all required parameters, data analysis will be performed in accordance with the intention-to-treat principle, additional per-protocol analysis will also be performed. Groups are, where appropriate, compared using an Independent Samples T-test, otherwise a Wilcoxon test, or Chi-square test. Pain scores will be analyzed using repeated measures analysis.

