### Endpoints

The primary endpoint of this study concerns the respiratory complications (i.e. infections) within two weeks after the operation. This is categorized as: grade 1) initial respiratory distress after operation with continuation of mechanical ventilation; grade 2) after successful detubation, clinical manifestation of respiratory infection caused by (broncho) pneumonia, confirmed by thorax X-ray or CT scan of the thorax and a positive sputum culture; and grade 3) other thoracic infections like post-operative empyema either caused or not by leakage from the gastric conduit necessitating drainage or reoperation [modified from Hulzebos et al., [11]]. Consequences for patients range from extensive physiotherapy, involving oxygen and specific antibiotics to intubation and mechanical ventilation. Furthermore, important respiratory deterioration after extubation, involving reintubation and mechanical ventilation will lead to the necessity of a CT scan of the thorax and abdomen, and thus endoscopic examination of the gastric tube and anastomosis in order to rule out a leakage.

The secondary endpoints are operation related events (e.g. duration of operation, blood-loss and conversion to open procedure in MIE group) and re-operations. Moreover, general morbidity (major and minor) is recorded. Minor complications are defined as wound infections, venous thrombosis or other. Major complications consist of- apart from respiratory complications- post-operative bleeding, anastomosis leakage, mediastinitis, and re-operations within the in-hospital period. Furthermore, post-operative recovery data are length of ICU and hospital stay (days), type and number of analgesics needed after operation, VAS-pain-score, return to fluid and normal diet, quality of life questionnaires (SF-36 and EORTC QLQ-OES18) [12], and quality of the specimen resected (length of specimen, number and location of lymph nodes resected, and circumferential resection margin). Also hospital mortality and readmissions are recorded. Furthermore survival will be analyzed.

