### Post-operative management

Patients in both groups will receive similar post-operative treatment. All patients will after surgery be admitted intubated at the intensive care unit (ICU). After stabilization and detubation, the patient will if indicated be admitted to the general surgical ward or to the medium care unit (MCU). In the first days after surgery analgesics are administered by the epidural route. In the event of epidural failure, post-operative pain will be treated intravenously by a 'patient controlled analgesia' (PCA); when necessary through a pump with morphine. Patients will be instructed about the PCA pump by an anesthesiologist and morphine doses will be noted. Patients will have a nasogastric tube in-situ for at least 5 days as some gastric conduit distension is expected. All patients will receive postoperative physiotherapy for breathing-exercises the day after surgery. To regain early mobilization, starting day 1, patients are encouraged to sit out of bed in the general surgical ward. Enteral feeding is commenced day 1 after operation through the jejunostomy and increased to optimal feeding at day 3. At day 5, after gastrographine swallow X ray, the nasogastric tube is retired and started with liquids. Normal diet can be progressively resumed while jejunostomy feeding is decreased. Patients will be discharged when they are able to eat normal food, can walk and are comfortable with oral analgesia. Delay to "social" reasons will be noted. Completion of the feeding over the jejunostomy may be continued after discharge. Patient follow-ups are carried out at the outpatient clinic at 6 weeks, 3 months, 6 months and 1 year after discharge. During these visits, the quality of life questionnaires (SF-36 and EORTC QLQ-OES18) will be completed. The regular follow-up will continue up to 5 years after surgery.

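### The primary endpoint runs to two weeks after surgery, but the stated clinical data collection ends at discharge, so infections between discharge and day 14 may be missed unless they lead to a recorded readmission

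*Protocol article*

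**What the plan says.** Four parts of the protocol article bear on this point.

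- **Window.** Under Endpoints: "The primary endpoint of this study concerns the respiratory complications (i.e. infections) within two weeks after the operation". The abstract gives the same two weeks.
- **Collection.** Under Data collection and statistics: "Data are collected daily until the day of discharge".
- **Discharge.** Under Post-operative management, oral intake begins early: "At day 5, after gastrographine swallow X ray, the nasogastric tube is retired and started with liquids". Discharge then follows recovery, not a fixed day: "Patients will be discharged when they are able to eat normal food, can walk and are comfortable with oral analgesia".
- **Next contact.** In the same section: "Patient follow-ups are carried out at the outpatient clinic at 6 weeks, 3 months, 6 months and 1 year after discharge". The one data item named for these visits is quality of life: "During these visits, the quality of life questionnaires (SF-36 and EORTC QLQ-OES18) will be completed".

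One further route for events after discharge appears among the secondary endpoints: "Also hospital mortality and readmissions are recorded". The text does not link readmissions to the primary endpoint or to its two-week window.

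The Background names a shorter hospital stay among the main advantages of minimally invasive surgery, and length of hospital stay is a secondary endpoint.

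**The concern.** A fixed window needs every patient to be observed to the end of it. Here the stated daily collection ends on a day that varies by patient. For anyone who goes home before day 14, the last part of the primary window is covered by no described assessment.

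The day on which collection ends is also an outcome of treatment. If patients leave earlier after MIE, as the article expects, the two arms are watched for different parts of the same window. A difference in how completely events are found can then enter the primary comparison as if it were a difference in events. What is at stake is the comparability of the primary endpoint between arms, more than the power of the trial.

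**Working it through.** **1. The plan's own figures.** Inputs from Power of the study: 57% (open), 29% (MIE), two-sided alpha 0.05, power 0.80. With the pooled-variance formula, no continuity correction, and mean rate (0.57 + 0.29)/2 = 0.43:

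n = [1.960 × √(2 × 0.43 × 0.57) + 0.842 × √(0.57 × 0.43 + 0.29 × 0.71)]² / 0.28² = 47.9, rounded up to 48 per arm.

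48 / (1 − 0.20) = 60 per arm. Both stated figures reproduce, and nothing below changes them.

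**2. Which events are exposed.** Taking the three grades under Endpoints in turn:

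- Grade 1 is continued mechanical ventilation after the operation. It occurs before discharge and cannot be lost.
- Grade 3 needs drainage or reoperation. After discharge it would mostly surface as a readmission, which is recorded.
- Grade 2 is a respiratory infection "confirmed by thorax X-ray or CT scan of the thorax and a positive sputum culture". It is exposed if it is imaged and cultured without a readmission, or treated at another hospital.

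**3. Size if late risk is equal in both arms.** The article gives no length of stay, so all inputs here are assumptions:

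- share discharged before day 14: 60–70% (MIE), 35–45% (open);
- risk of a qualifying event between discharge and day 14: 1–4% in either arm.

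Unseen events = share discharged × late risk.

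- MIE: 0.60 × 1% = 0.6 points to 0.70 × 4% = 2.8 points.
- Open: 0.35 × 1% = 0.35 points to 0.45 × 4% = 1.8 points.
- Difference in favour of MIE: (0.60 − 0.45) × 1% = 0.15 points to (0.70 − 0.35) × 4% = 1.4 points.

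With 60 per arm this is 0.09 to 0.84 of a patient, before readmission records recover any of it.

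**4. Direction if late risk is unequal.** Suppose late risk follows the planned rates, a ratio of 57/29 = 1.97 (also an assumption). At 1% late risk after MIE, it is 1.97% after open surgery:

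- Open: 0.35 × 1.97% = 0.69 points to 0.45 × 1.97% = 0.88 points.
- MIE: 0.60 × 1% = 0.60 points to 0.70 × 1% = 0.70 points.

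The open arm now loses as much or more in nearly every combination. The direction turns where the late-risk ratio, open to MIE, equals the ratio of discharge shares, MIE to open. That is between 0.60/0.45 = 1.33 and 0.70/0.35 = 2.0. Below 1.33 the error favours MIE, above 2.0 it works against MIE, and between them it depends on the discharge shares.

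**5. Effect on the test.** Assume no true difference, 43% in both arms, 60 per arm, and a two-sided pooled-variance test.

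| Loss of events | Spurious difference, points | Type I error |
|---|---|---|
| None | 0 | 0.050 |
| Upper end of step 3 | 1.4 | 0.053 |
| 5% of MIE events, none of open | 2.2 | 0.056 |
| 10% of MIE events, none of open | 4.3 | 0.076 |

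A spurious 1.4 points is 1.4/43 = 3.3% of events. The last two rows therefore lie beyond the range in step 3.

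**The case against.** The case on the other side has four parts.

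- **The collection sentence may only describe in-hospital frequency.** It does not say that all clinical data stop at discharge. Readmissions are recorded, clinic visits follow, and a research fellow monitors the data of every included patient. This stands in part. A reader might infer that infections after discharge are simply missed, and that such patients are scored as event-free. The documents support neither. Readmissions have a route into the data, and no text says how a patient discharged before day 14 is scored. What remains is that no stated step covers the rest of the window for a patient who is not readmitted.
- **The bias need not favour MIE.** This stands. A reader might infer a one-directional error from the expected shorter stay alone. That inference needs similar late risk in both arms, as under the null hypothesis. With late risk in the planned 57:29 ratio, the loss can be larger after open surgery.
- **The effect is small and every input is assumed.** This stands too. It limits the weight of the point, but it does not remove the mismatch.
- **A journal article condenses the full protocol, and the flowchart is not shown.** The full document may already provide a day-14 assessment. If it does, confirming that is enough. The point is still more than an omitted detail, because the article states both the window and the collection rule, and the rule does not cover the window.

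**Conclusion.** The point holds as a mismatch between two stated rules: a primary endpoint fixed at two weeks, and daily collection that ends at a recovery-dependent discharge, with no scheduled contact until 6 weeks later. Qualifying infections in between may be missed unless they lead to a recorded readmission, and grade 2 infections are the main ones exposed. Ascertainment can differ by arm because the article expects a shorter stay after MIE.

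The likely size is small: about 0.15 to 1.4 points in favour of MIE against a planned 28, given the assumed discharge shares and an equal late risk of 1–4%, before readmission capture. With higher late risk after open surgery the direction is uncertain. Confidence is high in the mismatch and low in the size and sign of the error. It is a cheap improvement and does not threaten the planned comparison.

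**What to change.** Ascertain the primary endpoint to day 14 in every patient, whatever the discharge date. For patients discharged earlier, use a short telephone call at day 14, or a question at the existing 6-week visit supported by records from any other hospital. Ask about each component of the endpoint that could arise after discharge, with its confirming imaging and culture where the definition requires them.

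State in the protocol that qualifying events found in readmission or outside-hospital records up to day 14 count in the primary endpoint, wherever the patient was treated. Record for each patient whether day-14 status was obtained, so that an unobserved end of window can be told apart from an event-free one.

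The cost is one extra datasheet item, a call or a question at a visit already planned, and a little chasing of outside records. The sample size stays at 48 evaluable and 60 randomized per arm, and clinical management is untouched.

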## Methods

### Study objectives

The TIME trial is prospective, multi-center, randomized study comparing traditional transthoracic esophageal resection with minimally invasive resection for esophageal cancer. Patients with resectable intrathoracic esophageal cancer are randomized for either (a) minimally invasive transthoracic esophageal resection in prone position or (b) traditional open transthoracic esophageal resection. Our hypothesis is that patients undergoing a minimally invasive esophagectomy have fewer morbidity, a shorter duration of the intensive care unit (ICU) admission and a better quality of life than following the traditional approach.

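### Quality of life is measured before surgery and at four later visits, but the analysis text states no baseline adjustment for it, which costs precision on a secondary endpoint named in the hypothesis

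*Protocol article*

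**What the plan says.** Under Study objectives, the hypothesis for the minimally invasive arm includes "a shorter duration of the intensive care unit (ICU) admission and a better quality of life than following the traditional approach". Under Endpoints, the "quality of life questionnaires (SF-36 and EORTC QLQ-OES18") are listed among the secondary, post-operative recovery outcomes.

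Data collection and statistics sets the schedule: "The quality of life questionnaires (SF-36 and EORTC-OES18) are completed by the patient starting preoperatively", and again at 6 weeks and at 3, 6 and 12 months after surgery, so each patient has one preoperative and four later scores per scale. The same section gives one general rule for analysis: "Groups are, where appropriate, compared using an Independent Samples T-test, otherwise a Wilcoxon test, or Chi-square test". One exception follows: "Pain scores will be analyzed using repeated measures analysis".

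No baseline covariate, change score or longitudinal model is named for quality of life anywhere in the article. Under Randomization, allocation takes place at the outpatient clinic once consent is given and is stratified by centre, because some heterogeneity between centres is expected.

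**The concern.** Quality of life and pain are both recorded repeatedly, but only pain is given a method suited to that. Quality of life is left to the general rule. A t-test or Wilcoxon test on follow-up scores makes no use of the preoperative score, although the trial collects it and it probably predicts later scores. Nor does it use centre, the stratification factor.

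What is at stake is precision. Under Power of the study, the trial is sized for respiratory infections only, so the precision of the quality-of-life comparison is whatever that sample happens to give. Adjusting for a score already collected is the cheapest way to improve it. The text also leaves open how the four follow-up visits are to be used together.

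**Working it through.** **1. The plan's own figure.** The only calculation in the article concerns the primary endpoint. It starts from "a difference in respiratory infections of 28% is found between the traditional open procedure (57%) and the MIE procedure (29"%), and adds: "This is based on a two-sided significance level (alpha) of 0.05 and a power of 0.80". With a mean rate of (0.57 + 0.29)/2 = 0.43 and pooled variance under the null:

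n = [1.960 × √(2 × 0.43 × 0.57) + 0.842 × √(0.57 × 0.43 + 0.29 × 0.71)]² / 0.28² = 47.9, so 48 per arm.

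Allowing for 20% exclusions, 48/0.8 = 60. Both stated figures reproduce. No power or precision is stated for quality of life.

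**2. Inputs for the quality-of-life check.** The sample is 48 evaluable or 60 randomised patients per arm (Power of the study). The correlation r between baseline and follow-up score is not in the documents, so I assume 0.3, 0.5 and 0.7. A true difference of 0.5 SD is assumed for the power figures, with a two-sided alpha of 0.05.

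**3. Variance relative to an unadjusted test on follow-up scores** (large-sample formulas, equal SD at baseline and follow-up):
- Adjusted for baseline (ANCOVA): 1 − r²
- t-test on change scores: 2(1 − r)
- Equivalent gain in patients from ANCOVA: 1/(1 − r²)

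| r | ANCOVA variance ratio | Variance cut | Equivalent gain in patients | Change-score variance ratio |
|---|---|---|---|---|
| 0.3 | 0.91 | 9% | 10% | 1.40 |
| 0.5 | 0.75 | 25% | 33% | 1.00 |
| 0.7 | 0.51 | 49% | 96% | 0.60 |

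The change score is always less precise than ANCOVA when r is below 1, because 2(1 − r) − (1 − r²) = (1 − r)². At r = 0.3 it is also worse than ignoring the baseline.

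**4. Effect at this trial's size.** The difference detectable with 80% power, in SD units, is (1.960 + 0.842) × √(2/n) × √(1 − r²). Power for 0.5 SD is Φ(0.5/√[(2/n)(1 − r²)] − 1.960).

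| | Unadjusted | r = 0.3 | r = 0.5 | r = 0.7 |
|---|---|---|---|---|
| Detectable difference, 48 per arm | 0.57 | 0.55 | 0.50 | 0.41 |
| Power for 0.5 SD, 48 per arm | 68.8% | 72.8% | 80.7% | 92.9% |
| Detectable difference, 60 per arm | 0.51 | 0.49 | 0.44 | 0.37 |
| Power for 0.5 SD, 60 per arm | 78.2% | 81.9% | 88.5% | 97.0% |

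These gains come from baseline adjustment at a single visit. Modelling the visits jointly adds little to them when all questionnaires are complete; it helps mainly when some are missing.

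**The case against.** The strongest reply is that no sentence assigns SF-36 or OES18 to a particular test. The general rule does not say which quantity is compared, so a t-test on change from the preoperative score would fit it and would use the baseline. The article also condenses a fuller protocol, and the model for a secondary questionnaire is often left to the SAP.

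Part of this stands. The text cannot be said to prescribe a test that ignores the baseline; it states no adjustment. But it is not silent either. It gives a general rule and one exception, and quality of life is not in the exception. The change-score reading does not remove the loss, as step 3 of the working shows.

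The reply is also right that the gain rests on an assumed r. All patients receive neoadjuvant therapy, and the article does not say whether the preoperative questionnaire comes before or after it. A low correlation is therefore possible, and at r = 0.3 the standard error falls by only 4.6% (1 − √0.91).

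A reader might go further in three ways that the documents do not support:
- **Chance baseline imbalance biases the comparison.** It does not: under randomisation the unadjusted test is valid, and its standard error already allows for such imbalance.
- **Patients who miss a visit will be dropped.** The article says nothing on missing questionnaires and states intention-to-treat analysis.
- **High early mortality makes dropout a major threat.** The only operative mortality figure is about 5% for the open transthoracic procedure (Background), and no 1-year mortality is given.

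**Conclusion.** The point holds as a loss of precision on a secondary endpoint. On its plain reading, the article compares quality of life by two-sample tests with no stated use of the baseline score or of centre. Baseline adjustment would cut the variance by 9% to 49% for r between 0.3 and 0.7. With 48 per arm, power for an assumed 0.5 SD difference would rise from 69% to between 73% and 93%.

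The size depends on r, which the documents do not give, and on a baseline score untouched by knowledge of the allocation. The tests remain valid without adjustment, and neither the sample size nor the primary analysis changes. The point is worth acting on because the remedy is cheap and the hypothesis names the outcome.

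**What to change.** In Data collection and statistics, extend the repeated-measures sentence to SF-36 and OES18. Analyse each scale with a linear mixed model containing treatment, visit, treatment-by-visit interaction, baseline score and centre, and report the adjusted difference between arms at each visit.

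Define the baseline as a questionnaire completed before the allocation is disclosed, and state where it falls relative to neoadjuvant therapy. The present wording fixes neither. A score given after the patient knows the arm may be influenced by that knowledge and should not be used as a covariate.

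The analysis change is one of wording, for data the trial already plans to collect. Fixing the baseline may require a change in when the first questionnaire is handed out, so the fix is not entirely free. The model also does not resolve scores cut off by death: it implicitly estimates scores for patients who have died, so deaths by visit should be reported beside the results.

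### Randomisation is stratified by centre, but the named two-group tests do not use centre; if centres differ, those tests are valid but somewhat conservative

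*Protocol article*

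**What the plan says.** The Randomization section of the protocol article gives both the design feature and its reason: "As some heterogeneity is expected, e.g. difference in type of neoadjuvant therapy protocol, randomization will be stratified for each center". The section on participating surgeons and clinics sets the number of strata: "Six European academic and non-academic centers will participate in the study". The Neoadjuvant therapy section adds that the choice between chemoradiotherapy and chemotherapy alone follows local practice.

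The section on data collection and statistics then fixes the comparisons: "Groups are, where appropriate, compared using an Independent Samples T-test, otherwise a Wilcoxon test, or Chi-square test". The only other method named there is for pain: "Pain scores will be analyzed using repeated measures analysis". No centre-stratified or centre-adjusted analysis appears anywhere in the article.

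The Power of the study section assumes respiratory infection in 57% of the open arm and 29% of the minimally invasive arm. It states: "This is based on a two-sided significance level (alpha) of 0.05 and a power of 0.80". From this it concludes that "two groups of 48 patients are needed", and then: "Estimating that approximately 20% of the patients may be excluded, 60 patients will be randomized per arm".

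**The concern.** Stratifying by centre with balanced allocation removes between-centre differences from the treatment comparison. A test that ignores centre still counts those differences in its standard error, which is then too large. The test rejects less often than its nominal level allows and is less powerful than one that uses the strata.

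The article gives reasons to think centre could matter. It expects heterogeneity, lets neoadjuvant treatment vary by centre, and says that complication rates may depend on surgeon experience, yearly volume and learning curve. With 48 evaluable patients per arm planned for 80% power, precision that the design has already bought is worth keeping. The article also commits to specific unstratified tests, so this is a stated choice and not a detail left open.

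**Working it through.** **Inputs from the article.** Rates 57% and 29%, two-sided alpha 0.05, power 0.80, 48 evaluable and 60 randomised per arm, six centres, stratification by centre.

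**Assumed, because the article does not give it.** The between-centre standard deviation (SD) of the outcome on the logit scale, varied from 0 to 1.5, and exact 1:1 balance within each centre.

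**Step 1: reproduce the planned size.** For two proportions with pooled variance under the null, the mean rate is (0.57 + 0.29)/2 = 0.43, and

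n = [1.96 × √(2 × 0.43 × 0.57) + 0.8416 × √(0.57 × 0.43 + 0.29 × 0.71)]² / 0.28² = 47.9, so 48 per arm.

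Inflation for 20% exclusions: 48/0.80 = 60. Both figures reproduce. Power of this unstratified comparison is 0.801 at 48 per arm and 0.882 at 60.

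**Step 2: simulate the effect of ignoring centre.** 100,000 trials per setting, six centres with 8 patients per arm each, normal centre effects on the logit scale, average rates held at 57%/29% (43%/43% under the null). Pearson chi-square is compared with Cochran-Mantel-Haenszel (CMH) stratified by centre, both without continuity correction.

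| Logit SD | SD of centre rates, open arm | Type I error, chi-square | Type I error, CMH | Power, chi-square | Power, CMH | Difference (points) |
|---|---|---|---|---|---|---|
| 0 | 0 | 0.050 | 0.050 | 0.802 | 0.802 | 0 |
| 0.25 | 0.060 | 0.048 | 0.049 | 0.807 | 0.808 | 0.1 |
| 0.5 | 0.116 | 0.046 | 0.049 | 0.812 | 0.820 | 0.8 |
| 0.75 | 0.164 | 0.039 | 0.048 | 0.819 | 0.840 | 2.1 |
| 1.0 | 0.205 | 0.034 | 0.049 | 0.825 | 0.863 | 3.7 |
| 1.5 | 0.267 | 0.025 | 0.050 | 0.831 | 0.902 | 7.1 |

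Unequal centre sizes (18, 10, 8, 5, 4 and 3 per arm) give nearly the same results. At 60 per arm with SD 1.0, type I error is 0.036 against 0.049 and power 0.904 against 0.928.

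**Step 3: check the type I error by hand.** Under the null with balance in six equal centres, the true variance of the difference is proportional to p(1 − p) − V, where V is the variance of the centre rates. The chi-square test uses, on average, p(1 − p) − V/6. With p = 0.43, p(1 − p) = 0.2451. Because 43% mirrors 57%, the SDs of centre rates in the table also apply here.

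- Logit SD 0.5: V = 0.116² = 0.0135. Ratio = 0.2316/0.2429 = 0.954. The effective critical value is 1.96/√0.954 = 2.007, so type I error is about 0.045 (simulated 0.046).
- Logit SD 1.0: V = 0.205² = 0.0420. Ratio = 0.2031/0.2381 = 0.853. The effective critical value is 1.96/√0.853 = 2.122, so type I error is about 0.034 (simulated 0.034).

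**Step 4: relax the balance assumption.** The article does not mention blocking. At the opposite extreme, simple 1:1 randomisation within each centre (60,000 trials, 96 patients, six centres), chi-square type I error is about 0.05 at every SD from 0 to 1.0, so the conservatism disappears. Power of CMH against chi-square is then 77.7% against 80.1% at SD 0 (2.4 points lower), 79.5% against 80.4% at SD 0.5 (0.9 lower), and 82.1% against 80.6% at SD 0.8 (1.5 higher). A separate run gave 77.5% against 80.0% at SD 0 and 84.1% against 80.5% at SD 1.0.

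**The case against.** The strongest reply is that no planned property fails. The sample size was set for an unstratified test, and that test keeps at least 0.80 power in every balanced setting. Type I error is not inflated, and under 1:1 balance within centre the risk difference is not biased. That stands: the loss is only relative to a more efficient test.

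The size is also assumed. For a logit SD of 0.5 or less, the loss is under one point. The article speaks only of some heterogeneity, with neoadjuvant protocol as its example. It does not say that outcomes will differ between centres or tie the anastomosis site to centre, and it restricts participation to high-volume hospitals with experienced surgeons precisely to limit such differences. This stands too, and it is why the result is given as a range.

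Further, the conservatism needs balance within centre. Restricted allocation is the natural reading of stratified randomisation, but it is not stated, and exclusions of about 20% could disturb the balance.

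Finally, this is a condensed article, and covariate adjustment is often left to fuller documents. That only softens the point, since naming unstratified tests sets the default.

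A reader might infer that the trial is underpowered, that every secondary analysis ignores centre, or that the confidence intervals are too wide. The article supports none of these. Power meets its target. The pain model's terms and the survival method are not specified, and no confidence-interval method is stated.

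**Conclusion.** The point holds as a mismatch between design and analysis with a modest efficiency cost. It is confined to the comparisons assigned to the chi-square, t-test and Wilcoxon test; the figures were worked out for the binary primary endpoint, and the same mechanism applies to the other two tests.

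Given within-centre balance and 48 patients per arm, the chi-square test runs at a true level of about 0.046 (logit SD 0.5) to 0.034 (SD 1.0) instead of 0.05, and gives up about 0.8 to 4 points of power against CMH. The loss is nil if centres do not differ and reaches about 7 points only at SD 1.5. The direction is firm under balance; the size rests on a between-centre variance that the article does not supply. The error is on the safe side, so a positive result from the planned test would not be undermined by it.

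**What to change.** In the statistics section, make the following changes:

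- **Primary endpoint:** a Cochran-Mantel-Haenszel test stratified by centre, reported with a Mantel-Haenszel risk difference.
- **Secondary endpoints now assigned to the t-test:** a linear model with centre as a factor.
- **Secondary endpoints now assigned to the Wilcoxon test:** the van Elteren (stratified Wilcoxon) test.
- **Very small centres:** pool them by a rule set in advance.
- **Sensitivity analysis:** keep the unadjusted chi-square test.

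The cost is a few lines of text and standard methods; 48 evaluable and 60 randomised per arm stay as they are. There is one possible price: if allocation within centre turns out to be unrestricted and centres barely differ, the stratified test can lose about 1 to 2.5 points of power. The sponsor should therefore confirm that allocation within centre is restricted when making the change.
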